#### Analysis of HIV, HBV, HCV, and HEV by next-generation sequencing

For suspected transfusion transmission of HIV, HBV, HCV, and HEV, both donor and recipient samples will be analyzed by sequencing as previously described [34] to confirm viral phylogenetic linkage of a TTI between donor and recipient. Donor and recipient samples will be compared when both are confirmed positive by initial testing (i.e., serology or nucleic acid). The sequences will be compared to reference sequences, and aligned and phylogenetic trees will be created. A seroconversion event will be considered to be linked if all available index and partner samples contain consensus sequences in a monophylogenetic group with a high bootstrap value (> 70).

#### *Plasmodium* allelic discrimination

If parasitemic blood is transfused to a non-parasitemic patient and parasitemia is identified post-transfusion, representative genes of the *Plasmodium* genome will be amplified for comparison between the donor and recipient to determine if the parasitemia was transfusion-transmitted or community-acquired. Donor and recipient samples will be compared when both are confirmed positive by initial testing (i.e., peripheral smear or nucleic acid). Allelic discrimination will be conducted using nested PCR of informative genome regions to further identify *Plasmodium* species. Sequencing of the representative genes will further discriminate between *Plasmodium* present in transfused WB products and in the patient post-transfusion [36]. Further high-resolution analyses based on genomic methods will also be considered [37]. Transfusion transmission will be assessed by matching up to three alleles present in donor and patient. The polymorphism of each allele is variable and will be considered in the interpretation of transfusion-transmitted malaria.

### Study power calculations

Table 1 shows the prevalence of TTIs contributing to the primary endpoint in donated blood and the expected number of infections per 1000 transfused participants in Uganda. We anticipate that participants will receive 1.5 units of WB on average [43] with ~ 50% of participants receiving at least two transfusions. Given the low infectivity of some TTIs, we further assume the risk of TTIs is independent of one another. We anticipate ~ 50% of transfusion recipients will have prior immunity to HHV-8 and HEV; in the absence of prior information, we hypothesize (conservatively) that immunity to these viral infections is independent. Under the above conditions, the expected cumulative incidence of at least one TTI by 10 weeks is 3.7% among control subjects (31 infections among 850 participants after factoring in 15% loss to follow-up). More specifically, we estimate that the 31 infections in the control arm will be comprised of 13 malaria (42%), 10 bacteria (31%), and 8 viral TTIs (26%). Because of uncertainties over the prevalence of disease in the donor population, the rate of infectivity, and 10-week return rates (conservatively ~ 15% LTFU expected), we have designed the study to enroll up to 2000 participants with 1000 subjects per trial arm over a 30-month period. There will be an interim analysis after 1000 study subjects have been enrolled. See stopping rules below.

**Table 1 Tab1:** Transfusion-transmitted infections in Uganda among blood donors. The table provides the prevalence of TTIs contributing to our primary endpoint in donated blood, sensitivity of screening methods (when used in Uganda), risk of a TTI given exposure to infected blood (i.e., infectivity), and the expected number of infections per 1000 transfused participants

Agent	Donor prevalence (%)	Screening method sensitivity (%)	Infectious units/1000 units of blood	Infectivity (%)	Expected number of infections/1000 transfused individuals+
HIV^#^	0.71	98	0.14	100	0.2
HBV^#^	2.41	98	0.48	75	0.5
HCV^#^	1.76	98	0.35	74	0.4
HEV*	0.6	No screening	6	75	6.8
HHV-8^	36.0	No screening	360	2.3	12.4
Malaria^∞^	5.0	No screening	50	20	15.0
Bacteria^≡^	1.5	No screening	15	50	11.3

^#^Seroprevalence data from Uganda Blood Transfusion Service in Kampala, Uganda, between April and June 2017

*HEV seroprevalence in Uganda is 47% [38]. However, RNA positivity with acute infection is ~ 0.6% [6]. Acute infection is most common among individuals in late adolescence, the primary blood donor age [39]

^HHV-8 seroprevalence in Uganda among late adolescence (primary blood donor age) is 36% [40]. The prevalence among recipients is ~ 50% [5]. There is an excess risk of HHV-8 seroconversion of 2.3% when transfused HHV-8 positive blood [5]

^∞^Malaria donor prevalence of 5% is a conservative estimate from data in Uganda [41]

^≡^Bacterial contamination prevalence derived from previous [42] and ongoing studies in Uganda of blood donors

+Expected number of infections in a population with no prior immunity

Figure 3 shows study power to detect a statistical difference in cumulative incidence of at least one TTI by 10 weeks between the intervention and control arms at varying levels of efficacy (*y*-axis; 50–90%) and cumulative incidence in the control arm (*x*-axis; 1–10%). Assuming a cumulative incidence of 3.7% in the control, an efficacy of 80% Mirasol PRT treatment (similar to the AIMS trial [29]), non-differential loss to follow-up of 15% by 10 weeks, we have 97% power to detect a statistically significant difference in cumulative TTI incidence between study arms (two-sided alpha = 0.05). Power to detect significant differences in cumulative incidence of malaria is 64%, viral infections 49%, and bacterial infections 51%.

**Fig. 3 Fig3:**
[figure not shown]
Study power based on Mirasol efficacy and cumulative TTI incidence

### Data collection, entry, and storage

Data is collected both on hard copy (paper) case record forms and soft copy as e-forms, checked for errors and consistency, and entered into a Research Electronic Data Capture (REDCap) database. Each participant is assigned a screening and enrolment number which are used as identifiers on study documents, instead of names, for confidentiality purposes. Participants’ study files and other source documents are stored under lock and key. All data entered in the REDCap system is stored on a server using a password-protected system.

### Analysis plan

A modified intention to treat (mITT) analysis will be performed to determine whether Mirasol PRT treatment of WB decreases the incidence of TTIs. The primary analysis will evaluate recipients who become positive for at least one of the targeted TTIs during the follow-up period and who received a blood unit with the confirmed presence of the corresponding infectious agent. This will estimate what proportion of new infections can be avoided by adopting Mirasol in transfusion medicine. A secondary analysis will be performed evaluating the reduction of incident TTI that is genetically linked to the transfused unit, which will estimate the efficacy of Mirasol at reducing TTI incidence.

*The ITT population* will consist of all randomized participants who undergo at least one study transfusion, independent of the outcome or successful completion of the procedure. Summaries by treatment group will be based on the randomized treatment assignment. The modified ITT (mITT) population consists of all those in the ITT population who have been assessed and have results for at least one TTI.

The per protocol (PP) population is defined as those who:
Received WB transfusions per the randomized treatment allocation during the 10-week study periodDid not receive any non-study blood products during trial participation prior to confirmation of presence or absence of TTIDid not receive any anti-malarial, anti-viral, or antibiotic treatment prior to confirmation of presence or absence of the malarial, viral, or bacterial TTI of interest, respectivelyHave no significant protocol deviations (including, but not limited to, inclusion- and exclusion criteria, and missing critical blood samples for TTI testing)

The study is powered to evaluate the combined incidence of all TTIs assessed, but the impact of Mirasol PRT on malaria and viral and bacterial infections will also be assessed separately. We expect 31 cumulative infections in the control arm giving us sufficient power (> 90%) to detect differences between study arms for our primary endpoint. A minimum of 23 infections from both arms is required in order to ensure adequate study power (> 90% power to detect an efficacy of 80%).

*The primary endpoint* is the cumulative incidence of one or more TTIs by 10 weeks among the mITT population. Log-binomial regression models will be used to estimate the relative risk reduction of incident TTI by 10 weeks associated with the Mirasol PRT. If the log-binomial model fails to converge, a Poisson model with robust variance estimation will be specified. Individuals lost to follow-up (including those who miss one or more study visits) will be censored from the primary analysis. Sub-analyses will be conducted separately for adults and children (< 18 years) and by sex. The primary analysis will also be stratified by the number of transfusions, with participants who received 1–2 transfusions analyzed separately from those who received ≥3 transfusions. Stratified analyses will also be conducted by admitting hospital. Efficacy will also be analyzed at each follow-up visit.

Sensitivity analyses will be conducted to assess whether or not there were important differences in demographics or health status between those with and without complete follow-up. In the event there are differences between those lost to follow-up and those who completed all study visits, inverse probability censoring weighting and stratification will be used to assess potential selection biases [44]. Similar calculations will be made if there is differential follow-up. A sensitivity analysis will be performed among participants who completed their 10-week follow-up visit, regardless of any previously missed visits. An additional analysis will be performed restricted to participants who are negative for all bacterial, viral, and parasitic infections at baseline. A final sensitivity analysis will be performed among participants who attended at least one follow-up visit and test results for all TTI of interest are available. All analyses will be repeated in the ITT and PP populations.

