**Fig. 2 Fig2:**
[figure not shown]
Donor blood and recipient evaluation

Individuals who require additional transfusions are followed as above as long as they receive the additional transfusions within the first 6 weeks of their initial transfusion (i.e., they will be evaluated at 48 h, day 7, and day 28 of both the first and any subsequent transfusions). The visits are combined if they fall within the same window. However, once the individual reaches week 10 from the initial enrollment and transfusion, their follow-up ends. If individuals require transfusion support for transfusions received after the first 6 weeks of study participation, they still receive study blood transfusions as per their randomization until study exit at 10 weeks but do not have additional follow-up visits. To encourage adherence to study procedures, participants are compensated for their time and transportation for each scheduled visit. Participants are also eligible to withdraw from the trial at any stage.

In case of a transfusion reaction, the transfusion is stopped and the patient evaluated. After the relevant checks and investigations have been done, the transfusion may or may not be restarted. The participant’s trial arm is maintained for all future transfusions. Participating in the trial should not affect the usual patient care or require any alteration to concomitant medication.

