### Intervention outcomes

The primary endpoint of this study is the incidence of any pre-defined viral, bacterial, or parasitic TTI: HIV, HBV, HCV, HEV, HHV-8, bacteria, or malaria in a previously negative recipient for the specific TTI as indicated by changes in laboratory findings at day 2, day 7, week 4, or week 10 after the first transfusion. A TTI will only be ascribed when both the donor unit and recipient have the exact same pathogen as confirmed by specialized laboratory testing.

In addition, the clinical effectiveness of Mirasol-treated WB products compared to standard WB products in recipients will be evaluated by the following:
Incidence and characteristics of acute transfusion reactions as defined by CDC Hemovigilance [31]Change in hemoglobin level post-transfusion compared to pre-transfusionDelayed transfusion reactions/neoantigenicity
i)Incidence of an amnestic RBC alloantibody as detected by a positive direct antiglobulin test (DAT) when participants are evaluated for transfusion reactionii)Incidence of new red cell alloantibodies post-transfusion (positive antibody screen at 10 weeks)Incidence of treatment-emergent adverse events (TEAE) and treatment-related adverse events

In order to assess the primary and secondary outcomes, the following laboratory tests will be performed (Fig. 1):

● Complete blood counts (CBCs)

● RBC antibody screen and direct antiglobulin test (DAT). The antibody screen will be used to determine new RBC alloantibody identification. If there is a suspected acute hemolytic transfusion reaction, a DAT will be performed. If the DAT is positive, antibody identification will be performed to determine whether it is a RBC alloantibody or a new antibody due to Mirasol PRT [32, 33].

● Bacteria: Cultures will be performed for both the donor unit and recipients. A TTI will only be ascribed when both the donor unit and recipient have the exact same genus and species.

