● Viral TTIs: Serology assays for HIV (antigen and antibody combination), HBV (HBsAg, HBcAb), HCV (anti-HCV), HEV (IgG, IgM, and antigen), and HHV-8 (based on epitopes in open reading frames 73 and K8.1) will be performed on both donor units and recipients. The recipients will be evaluated at the last follow-up time point (week 10). If the recipient is positive, the other time points (i.e., enrollment (baseline), 48 h, day 7, and week 4) will subsequently be evaluated. HBV, HCV, HEV, and HIV nucleic acid testing (NAT) will also be performed among all donors and also for recipients at week 10, similar to serology testing.

● Malaria: Peripheral smears (thin and thick) will be performed among donor samples and on recipients at 48 h, day 7, and week 4. PCR assays will also be conducted to increase sensitivity [35]. The reading of the smears and PCR tests will be done retrospectively on stored samples and the results will not be available before transfusion. Two positive malaria PCR tests in the recipient post-transfusion samples are required to ascribe a malaria infection.

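### The per-protocol treatment exclusion is tied to confirmation of a TTI rather than to sample dates, so supportive analyses can lose true malaria or viral events that were treated before they were read

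*Protocol article*

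**What the plan says.** All references are to the protocol article.

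- **PP rule (Analysis plan).** A PP participant must not have received "any anti-malarial, anti-viral, or antibiotic treatment prior to confirmation of presence or absence of the malarial, viral, or bacterial TTI of interest". The criterion closes with *respectively*, so an anti-malarial counts only against malaria, and likewise for the other two classes. The criterion on non-study blood products uses the same anchor.
- **Malaria (Intervention outcomes).** "The reading of the smears and PCR tests will be done retrospectively on stored samples and the results will not be available before transfusion". Also: "Two positive malaria PCR tests in the recipient post-transfusion samples are required to ascribe a malaria infection". Recipient samples are taken at 48 h, day 7 and week 4.
- **Viruses (Intervention outcomes).** Recipients are tested first on the week-10 sample. Earlier samples are tested only if that one is positive.
- **Bacteria (Intervention outcomes).** "Cultures will be performed for both the donor unit and recipients". Nothing describes these as retrospective or done on stored material.
- **Usual care (Assignment of intervention, text after Fig. 2).** "Participating in the trial should not affect the usual patient care or require any alteration to concomitant medication".
- **Role of the PP set (Analysis plan).** The primary endpoint is analysed in the mITT population, which has no treatment exclusion. Then: "All analyses will be repeated in the ITT and PP populations".

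**The concern.** The evident purpose of the rule is to drop participants whose drug treatment could hide an infection from the tests. For that purpose the relevant date is when the sample was drawn. The rule uses confirmation instead, and for malaria that can fall long after the last sample, at a time set by the laboratory.

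A recipient who becomes ill with transfusion malaria and is treated under usual care has then been treated before confirmation, and is removed because of the outcome being counted. An uninfected recipient who takes an anti-malarial after the last malaria sample, but before the stored samples are read, is removed although the drug could not have affected any result.

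PP membership would therefore depend on treatment that the outcome can cause and on laboratory scheduling. At stake are the events, precision and interpretability of the PP repeats, including the separate malaria and viral analyses.

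**Working it through.** **1. The rule applied to the test schedule.**

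| Case | Samples | Treatment | Date of result | Date of sample |
|---|---|---|---|---|
| Malaria TTI | PCR-positive at 48 h and day 7 | anti-malarial day 10 | excluded | kept |
| Malaria TTI | PCR-positive at 48 h and day 7 | anti-malarial day 5 | excluded | excluded if the second PCR is the confirming one |
| Viral TTI | positive at week 4 and week 10 | anti-viral between them | excluded | depends on which sample counts |
| No malaria, one transfusion | last sample week 4 | anti-malarial week 8, before reading | excluded | kept |

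The last two columns show the outcome when *confirmation* means the date of the result or the date of the sample. The text fixes neither. Because two PCRs are required, the sample-date reading does not settle every case.

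**2. Inputs (Study power calculations; Analysis plan).** Control incidence 3.7%; efficacy 80%; 850 evaluable per arm; two-sided alpha 0.05; 31 expected control events (13 malaria, 10 bacterial, 8 viral); a stated minimum of 23 events over both arms.

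**3. The plan's own power.** Power = Φ(d/SE − 1.96), with d = p_C − p_M and SE = √{[p_C(1 − p_C) + p_M(1 − p_M)]/850}.

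p_C = 0.037, p_M = 0.2 × 0.037 = 0.0074, d = 0.0296, SE = 0.00711. Power = Φ(4.16 − 1.96) = Φ(2.20) = 98.6%. The plan states 97%; a continuity correction gives about 97.8%. The inputs are confirmed.

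**4. Loss of malaria cases from the PP set.** Let f be the share of malaria cases removed, equal in both arms. The documents do not give f, so it is an assumption. Removed cases are taken to leave the combined endpoint. The denominator is kept at 850.

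Control events = 31 − 13f; Mirasol events = 0.2 × (31 − 13f); total = 37.2 − 15.6f.

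| f | Control | Mirasol | Total | Power |
|---|---|---|---|---|
| 0 | 31.0 | 6.2 | 37.2 | 98.5% |
| 25% | 27.75 | 5.55 | 33.3 | 97% |
| 50% | 24.5 | 4.9 | 29.4 | 96% |
| 75% | 21.25 | 4.25 | 25.5 | 93% |
| 100% | 18.0 | 3.6 | 21.6 | 88% |

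Example, f = 50%: p_C = 24.5/850 = 0.0288, p_M = 4.9/850 = 0.0058, d = 0.0231, SE = 0.0063. Power = Φ(3.66 − 1.96) = Φ(1.70) = 96%.

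The total falls below 23 only when f exceeds (37.2 − 23)/15.6 = 91%.

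**5. Malaria and viral cases together (21 of 31).** Total = 1.2 × (31 − 21f). At f = 50% this is 24.6 events and 92% power; at 75%, 18.3 events and 82%.

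**6. Relative risk.** With equal f, efficacy stays at 1 − 0.2 = 80%. With unequal shares of malaria cases removed it moves either way:

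- 50% control, 25% Mirasol: 1 − 5.55/24.5 = 77%.
- 25% control, 50% Mirasol: 1 − 4.9/27.75 = 82%.

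No passage supports either split.

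**The case against.** - **Only a supportive population is touched.** This stands. The mITT set keeps every treated TTI, the interim test concerns the primary outcome, and no power is claimed for the PP set. The power figures above measure lost precision in a repeat analysis, not a threat to the trial's main test.
- **Confirmation could mean the sample date, and the SAP may say so.** It may; Trial status says the SAP was still being finalized. But the article states this criterion and its anchor, so the point is how a stated rule is worded, not a missing detail. The day-5 case shows that the lenient reading still leaves a gap.
- **Late confirmation is not shown for all three classes.** This stands. Stored-sample reading is stated only for malaria (13 of 31, 42%), and viral testing is deferred by design. Bacterial events are not counted as confirmed late here.
- **Bias is not shown.** This stands. A reader might infer that treated TTIs leave mainly from the control arm and so pull PP efficacy towards no effect. More control cases would leave simply because more are expected there, and equal proportional loss leaves the ratio unchanged. The staff who transfuse and monitor are blinded, and no treated shares are given.

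**Conclusion.** The rule is badly anchored and should be reworded, but its reach is limited to the PP repeats. Read literally, it removes true malaria and viral TTIs because they were treated, and some uninfected participants whose samples no drug could have affected.

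On the plan's figures, removing half to all of the malaria cases in both arms costs about 8 to 16 of 37 expected events and takes power to between 96% and 88%. This rests on assumed shares, on equal loss in both arms and on the literal reading.

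Two stronger conclusions do not follow. The main efficacy result does not lose these events, because the mITT set has no treatment exclusion. PP efficacy is not shown to be biased in a particular direction.

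**What to change.** Reword the PP criterion so that it refers to sample collection dates, separately for each class:

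1. Exclude a participant for a TTI class only if a matching drug was given after the first study transfusion and before collection of the samples that determine status for that class.
2. For a recipient with a TTI, the closing date is the first positive sample. For malaria it is the first of the two qualifying PCR-positive samples.
3. For a recipient without one, it is the last scheduled sample for that class, counted from the last transfusion that triggers follow-up visits. The 48 h, day 7 and day 28 visits repeat after later transfusions in the first 6 weeks, and about half of participants are expected to have at least two transfusions.
4. State that treatment given after a qualifying positive sample was collected does not remove the event, whenever the sample is read.
5. Use the same sample-date anchor for the criterion on non-study blood products.

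The cost is a few sentences. Drug and sample dates are the only data required, and no patient care changes.

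One downside should be stated: the exclusion window remains longer for non-cases than for cases, so PP incidence may be slightly raised. Report the number excluded under this rule by arm and TTI status so that readers can judge it.

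### The primary analysis is set in the mITT population but leaves out anyone who misses a visit, so TTIs established from samples already taken are dropped

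*Protocol article*

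**What the plan says.** All of this is in the Protocol article; the first three items come from its Analysis plan section.

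- Population: "The modified ITT (mITT) population consists of all those in the ITT population who have been assessed and have results for at least one TTI". Attendance is not a condition.
- Endpoint and model: the primary endpoint "is the cumulative incidence of one or more TTIs by 10 weeks among the mITT population". The treatment effect on it is a relative risk from a log-binomial model, with a robust-variance Poisson model if the first does not converge.
- Missed visits: "Individuals lost to follow-up (including those who miss one or more study visits) will be censored from the primary analysis".
- Timing (Intervention outcomes): a TTI is judged "as indicated by changes in laboratory findings at day 2, day 7, week 4, or week 10 after the first transfusion". Malaria smears are listed for 48 h, day 7 and week 4, and two positive PCRs are needed. Viral testing starts with the week 10 sample and goes back to earlier samples only if that one is positive. Assignment of intervention places the blood draw for bacterial culture within 48 h of each transfusion.
- Loss allowance (Study power calculations): 15%, given alongside uncertainty over "the rate of infectivity, and 10-week return rates".

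**The concern.** The same section gives the primary analysis two different populations. Under the mITT definition, a recipient with a donor-matched bacterial culture at 48 h belongs in the analysis as an event. Under the missed-visit sentence, that recipient leaves it after missing week 10, or any other visit.

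Missing a visit is unlikely to be unrelated to outcome. The Discussion expects losses through death because many recipients are very sick, and it reports follow-up difficulties during the pandemic. Participants transfused again within the first six weeks have further 48 h, day 7 and day 28 visits unless windows coincide. Those exposed to more donor units therefore tend to have more visits to miss. At stake are the absolute incidence, which is the stated endpoint, and the randomised comparison, which becomes one among complete attenders. An interim look that uses the same analysis inherits the rule.

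**Working it through.** **1. What censoring means here.** A log-binomial or Poisson risk model takes one yes/no outcome per person. It cannot use follow-up up to a censoring time, so a person censored from it is absent from numerator and denominator. The plan supports this reading: an analysis of week 10 completers that ignores earlier missed visits is listed separately, as a sensitivity analysis.

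**2. Which events are exposed.** Study power calculations expects 13 malaria, 10 bacterial and 8 viral TTIs in the control arm. Malaria and bacteria make up (13 + 10)/31 = 23/31 = 74%. Both can be established before week 10. The 8 viral events are exposed in the other direction: found at week 10, then dropped if an earlier visit was missed.

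**3. The plan's own figures.** Inputs: control risk 3.7%, efficacy 80% (so 0.037 × 0.20 = 0.74% with Mirasol), 850 per arm, two-sided alpha 0.05.
- Control events: 850 × 0.037 = 31.45, against 31 stated.
- Pooled two-proportion power: mean risk 0.0222. Φ[(0.0296 − 1.96 × √(2 × 0.0222 × 0.9778/850)) / √((0.037 × 0.963 + 0.0074 × 0.9926)/850)] = Φ(2.19) = 98.6%. With continuity correction it is 97.9%. The stated 97% is reproduced closely enough.

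**4. Events dropped at the planned loss.** Per 1000 control participants, 150 are lost. At average risk they include 150 × 0.037 = 5.55 TTIs, of which 5.55 × 23/31 = 4.1 are malaria or bacterial. How many were established before loss depends on when people leave, so the range is 0 to about 4. Exclusions for a missed earlier visit come on top; the article gives no rate for them.

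**5. When this becomes bias.** Let r be the share of TTI cases retained, with 85% of non-cases retained. For a small risk, the estimated control incidence is about 3.7% × r/0.85. It is understated only if r is below 0.85. The estimated relative risk is about 0.20 × (r in Mirasol arm)/(r in control arm), which moves only if case retention differs by arm. The documents give no value for r.

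**6. Power under the rule.** Assume 15% loss at week 10 and an independent miss rate m at each of the three earlier sampling visits (m is an assumption). The share attending all visits is 0.85 × (1 − m)³.

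| m | n per arm | Power, pooled | Power, continuity-corrected |
|---|---|---|---|
| 0% | 850 | 98.6% | 97.9% |
| 2% | 800 | 98.1% | 97.1% |
| 5% | 728 | 97.0% | 95.6% |
| 10% | 619 | 94.3% | 91.8% |
| 15% | 522 | 90.2% | 86.0% |

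Repeat transfusions add visits, so the real share may be lower than the table shows, although visits falling in the same window are combined.

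**7. Why a half fix fails.** Suppose the 4.1 events are kept while event-free lost participants are still dropped. Incidence becomes (31.45 + 4.12)/(850 + 4.12) = 35.57/854.12 = 4.2%, against a true 3.7%. Keeping events therefore requires keeping the event-free as well.

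**The case against.** The strongest reply is that the plan already looks at missing follow-up from several sides:

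- inverse probability weighting if those lost differ from completers, or if follow-up differs by arm;
- an analysis of week 10 completers;
- an analysis of those with at least one visit and all TTI results;
- efficacy at each visit;
- repeats in the ITT and PP populations.

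This matters, but none of it puts the events back in the primary result. The weighting is conditional ("In the event there are differences between those lost to follow-up and those who completed all study visits, inverse probability censoring weighting") and reweights completers. The week 10 analysis still loses early events in people who miss week 10. The one-visit analysis requires results for every TTI.

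It is also fair that an event-free person without the 48 h culture or week 10 viral tests cannot simply be called negative. That justifies special handling of such people, but not removal of people with an established event. A SAP might settle events before dropout, but the article states a rule, and as written the rule excludes them.

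A reader might infer more than the documents support:

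- **That power is compromised.** It is not, except mildly at the most pessimistic attendance in the table. The per-visit rates are assumptions.
- **That the dropped TTIs were already confirmed when the person left.** Malaria smears and PCR are read retrospectively. The most that can be said is that the TTI can be established from samples already taken.
- **That every malaria and bacterial TTI shows by week 4.** Transfusions up to six weeks are followed to day 28, which can reach week 10.
- **That about 4 lost events prove bias.** That figure assumes equal risk, so numerator and denominator shrink together.
- **That the ITT repeat reduces to the same complete attenders.** The article does not say whether the exclusion carries over.

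**Conclusion.** The concern holds as a contradiction between two stated rules, with a real consequence if the missed-visit sentence is followed. Established TTIs, chiefly bacterial and malaria, leave the primary analysis because some other visit was missed. At the planned 15% loss and average risk this is 0 to about 4 bacterial or malaria events per 1000 control participants, against 31 expected control events. It is more if cases die or drop out more often, which the Discussion makes plausible but the documents do not quantify. Absolute incidence is then understated. The relative risk moves little if case retention is the same in both arms, and nothing in the plan guarantees that. That removal extends to participants who die is a plausible reading, since they miss later visits, but the sentence does not mention death. The problem is selection and loss of observed events; power is a side issue.

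**What to change.** Reconcile the two statements in the Analysis plan:

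1. Make the primary set the mITT population as defined, and count every TTI established from available samples as an event whatever other visits are missed.
2. Keep event-free participants with incomplete follow-up in the analysis through pre-specified inverse probability of censoring weighting, or a cumulative-incidence estimate, and not only when a difference is found. Without this step, incidence is biased upward.
3. Keep complete attenders as a sensitivity analysis.
4. State that the 15% allowance is a 10-week return rate and not the share missing any visit.

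The cost is a little more analysis work and reliance on a weighting model that the plan already names. No new data are needed. The article reports more than 700 of 2000 recruited and a SAP only then being finalised; the change is best made before the interim analysis, which waits for 10-week data on the first 1000.
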